| Key Inclusion Criteria | 
 
1. Haemoglobin <5.0g/dl or PCV <15%, or requirement for blood transfusion for other clinical reasons on or during admission to the hospital
 
2. Age between 4 months (inclusive) and 59 months (inclusive)
 
3. Body weight >5kgs
 
 
Screening (in-hospital)
 
 
1. Fulfilled the pre-study screening eligibility criteria
 
2. Clinically stable, able to switch to oral medication
 
3. Subject completed blood transfusion(s) in accordance with routine hospital practice
 
4. Able to feed (for breastfed children) or eat (for older children)
 
5. Absence of known cardiac problems
 
6. Provision of informed consent by parent or guardian
 
 
Randomization (at discharge)
 
 
1. Fulfilled screening eligibility criteria
 
2. Still clinically stable, able to take oral medication, able to feed (for breastfed children) or eat (for older children) and able to sit unaided (for older children who were able to do so prior to hospitalization)
 
 |
| Exclusion Criteria     | Pre-study screening                                                                                                                                                                                                                                                                                                                                                                                                                                                                                                                                                                                                                                                                                                                                                                                                                                                                                                                                                                                                                                                                                                                                                                     |

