|                        | 
 
1. Recognised specific other cause of severe anaemia (e.g. trauma, haematological malignancy, known bleeding disorder)
 
2. Known sickle cell
 
3. Child will reside for more than 25% of the 3.5months study period (i.e. 3 weeks or more) outside of catchment area
 
 
Enrolment in the study (t=0) at discharge
 
 
4. Previous enrolment in the present study
 
5. Known hypersensitivity to study drug
 
6. Sickle cell disease
 
7. Known need at the time of enrolment for concomitant prohibited medication during the 14 weeks PMC treatment period.
 
8. On-going or planned participation into another clinical trial involving on-going or scheduled treatment with medicinal products during the course of the study (3.5 months from enrolment)
 
9. Known need, or scheduled surgery during the course of the study (3.5 months)
 
10. Suspected non-compliance with the follow-up schedule
 
11. Known heart conditions, or family history of congenital prolongation of the QTc interval
 
 
HIV infection and cotrimoxazole prophylaxis are not exclusion criteria
 |
| Primary Outcome        | 100% of PMC drugs uptake (defined as administration of all 3-day treatment courses, given 2, 6 and 10 weeks after discharge) assessed by unannounced spot checks                                                                                                                                                                                                                                                                                                                                                                                                                                                                                                                                                                                                                                                                                                                                                                                                                                                                                                                                                                                                                                                                                    |

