## 4.2 Narrative Protocol Summary

**Title:** Malaria Chemoprevention with monthly treatment with dihydroartemisinin-piperaquine for the post-discharge management of severe anaemia in children aged less than 5 years in Malawi: A 3-year, single site, parallel-group, five-arm cluster randomised trial of community versus health facility-based delivery mechanisms with or without mobile phone SMS reminders

**Short Title:** Post-discharge Malaria Chemoprevention Delivery (PMC) study

**Background and rationale:** Children hospitalised with severe anaemia in Africa are at high risk of readmission or death within 6 months after discharge. No strategy specifically addresses this post-discharge period. In Malawi, 3 months of post-discharge malaria chemoprevention (PMC) with monthly 3-day treatment courses of artemether-lumefantrine (AL) in children with severe malarial anaemia prevented 31% of deaths and readmissions. The effect was in addition to the effect of insecticide-treated bednets. There is now need to design and evaluate effective delivery mechanism for PMC within the health system.

**Objectives:** The primary objective of the trial is to determine the optimum PMC delivery mechanism by comparing community- versus health facility-based strategies in order to inform policy

**Study Type:** This is a single-centre, matched, cluster randomized, 5-arm, factorial design trial comparing the uptake of PMC-DHP delivered through health facility or community-based approaches with or without SMS/HSA reminders.

**Site:** 90 villages in the catchment areas of Zomba Central hospital in southern Malawi

**Study Population:** Inclusion criteria: convalescent children aged less than 5 years and weighing >5 kg admitted with severe anaemia (haemoglobin <5g/dL / Ht <15%); clinically stable, able to take or switch to oral medication; post-transfusion Hb >5g/dL. Exclusion criteria: blood loss due to trauma, malignancy, known bleeding disorders or sickle cell trait, known hypersensitivity to study drug, known heart conditions, non-resident in study area, previous participation in study, known need at enrolment for prohibited medication and scheduled surgery during the course of the study. HIV infection and cotrimoxazole prophylaxis are not exclusion criteria

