| Period                                                                              | Pre-PMC                                             | PMC                                                                                                                                                                                                                          |
| Trial intervention                                                                  | AL near discharge, all arms                         | Gp1: PMC Drugs at discharge + No SMS Reminder
Gp2: PMC Drugs at discharge + SMS Reminder
Gp3: PMC Drugs at discharge + HSA Reminder
Gp4: PMC Drugs at OPD + No SMS Reminder
Gp5: PMC Drugs at OPD + SMS Reminder |
| Rescue Rx acute malaria                                                             | Oral QN, 7 days                                     | AL, 3 days                                                                                                                                                                                                                   |
| Treatment for severe malaria                                                        | Parenteral artesunate / quinine and oral AL, 3 days |                                                                                                                                                                                                                              |

An end of study assessment will be done 14 weeks (3.5 months) after discharge.  
 AL=artemether-lumefantrine. PMC=Post-discharge Malaria Chemoprevention.  
 DP=dihydroartemisinin-piperaquine. QN=quinine

Table 2: Study Design and Schedule of Assessment

| Phase                       | Screening Phase         |                               | In-patient Hospitalisation phase | Enrolment & Randomisation | PMC Treatment Phase
12 weeks period from 2-14 weeks |                                     |                                      |                          |          |          |           |           |           | Post-intervention |
|-----------------------------|-------------------------|-------------------------------|----------------------------------|---------------------------|--------------------------------------------------------|-------------------------------------|--------------------------------------|--------------------------|----------|----------|-----------|-----------|-----------|-------------------|

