##### 8.7.4.1 Assignment of study IDs

Pre-screened subjects who meet all eligibility criteria will be issued a study subject number during this visit. Once issued the study subject number they will be considered as 'enrolled'. This number is the subject's unique identifier and used to identify the subject on the CRFs. Subject numbers will be assigned strictly sequentially as subjects enter the study. Once a number has been assigned no attempt will be made to use that number again, for example even if a subject discontinues or is a screening failure.

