#### 8.7.4.3 Clinical assessment:

After consent is obtained and the subject's eligibility is confirmed the subject's demographic data will be recorded in the CRF, and all relevant clinical information, including the previous and current medical history, and laboratory information copied from the hospitals clinic and laboratory notes to the CRF (see CRF for details). A further clinical examination (including anthropometrics) will be performed and a medical history taken that will serve as the baseline examination and captured on the CRF.

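### The enrolment lists in 8.7.4.3–8.7.4.4 omit the heart/QTc exclusion stated in 4.1 and apply the sitting rule to every child, and no text says which list governs

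*Protocol*

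**What the plan says.** **Summary sections.** The protocol's section 4.1 handles cardiac risk twice. Item 5 of its in-hospital screening criteria reads "Absence of known cardiac problems", and exclusion 11 at enrolment reads "Known heart conditions, or family history of congenital prolongation of the QTc interval". Section 4.2 lists among its exclusions "known hypersensitivity to study drug, known heart conditions, non-resident in study area". On sitting, the randomisation criteria in 4.1 require the child to be "able to sit unaided (for older children who were able to do so prior to hospitalization").

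**Body.** The pre-study lists printed under 8.7.4.3 have three inclusions and one exclusion, the latter on other causes of anaemia. Section 8.7.4.4 has six inclusions and ten exclusions. Inclusion 5 there demands unaided sitting with no qualifier. Exclusions 8 and 10 are the same item, on expected poor compliance with follow-up. The lower age limit is 4 months.

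**Link between them.** Section 8.7.4.1 says: "Pre-screened subjects who meet all eligibility criteria will be issued a study subject number during this visit". It does not name a list, and I found no statement of precedence elsewhere.

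**The concern.** Section 14.5.4 names dose-dependent QTc prolongation as the main safety concern with piperaquine. A history-based exclusion is the obvious safeguard: the schedule of assessments in Table 2 shows no ECG, and under 8.6.2 the three discharge arms take every dose at home. That safeguard stands in the two summary sections and is missing from the section that describes enrolment.

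The sitting rule errs in the other direction. An infant of 4 months or more who had never sat unaided meets the 4.1 criteria and fails 8.7.4.4. What is at stake is wrong enrolment and wrong refusal. The sample size and the analysis are not involved.

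**Working it through.** The plan states no figure for this point, so the check is a comparison of the lists.

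**Count of items.** Body lists: 3 + 1 (pre-study, under 8.7.4.3) + 6 + 10 (8.7.4.4) = 20, or 19 distinct items because exclusion 10 repeats exclusion 8.
- Heart conditions: two items in 4.1 plus one in 4.2 = 3 mentions, against 0 of 20 in the body.
- Family QTc history: 1 mention (4.1, exclusion 11), against 0 of 20.

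**Where the item was lost.** The 4.1 in-hospital screening list and the 8.7.4.4 inclusion list each have six entries and match at entries 1 to 4 and 6. At entry 5, the cardiac item in 4.1 has become the sitting item in 8.7.4.4. This looks like a drafting loss.

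**Outcome by child** (otherwise eligible, needing no prohibited drug):

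| Child | 4.1 alone | 8.7.4.3–8.7.4.4 alone | Both together |
|---|---|---|---|
| Known heart condition | excluded | admitted | excluded |
| Family QTc history only | excluded | admitted | excluded |
| Infant of 4 months or more who could not sit before admission | admitted | refused | refused |

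Applying both lists closes the cardiac gap but does not deliver the sitting rule of 4.1.

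**Does other text restore the exclusion?**
- Inclusion 1 of 8.7.4.4 points back to the pre-study lists, which have no cardiac item.
- Exclusion 6 of 8.7.4.4, with the prohibited list in 8.7.7.2, catches children known to need certain drugs. It says nothing about diagnosis or family history, and 4.1 itself keeps the two apart (items 7 and 11).
- In 8.7.4.3, once eligibility is confirmed, "A further clinical examination (including anthropometrics) will be performed and a medical history taken". That is after the decision.
- Section 8.8 allows discontinuation for a screening error or for safety. Both act after enrolment, and a screening error presupposes knowing which list applies.

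**Related differences to settle in the same edit.**
- Fever and use of the study drug since screening are exclusions only in 8.7.4.4.
- The bar on other trials and surgery covers 3.5 months in 4.1 and 6 months in 8.7.4.4.
- Section 4.2 excludes sickle cell trait, while 8.7.4.3 names the disease. Section 4.2 also asks for a post-transfusion haemoglobin above 5 g/dL, which neither list contains.
- Residence: 4.1 excludes if "Child will reside for more than 25% of the 3.5months study period (i.e. 3 weeks or more) outside of catchment area". Table 1 equates the periods: "An end of study assessment will be done 14 weeks (3.5 months) after discharge". So 14 × 7 = 98 days and 0.25 × 98 = 24.5 days = 3.5 weeks, whereas 3 weeks is 21/98 = 21.4%. Section 8.7.6.2 uses 1 month or more, that is 28/98 = 28.6% to 31/98 = 31.6%. Exclusion 5 of 8.7.4.4 sets no threshold and refers to 6 months. A child planning 26 days away is excluded by 4.1 (26 > 24.5) but not by 8.7.6.2 (26 < 28).

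**The case against.** The best reply is that leaving an item out of one list does not contradict its presence in another. Section 8.7.4.1 requires all eligibility criteria to be met, so a reader who applies every list keeps the heart/QTc child out. This stands. The cardiac half is an omission that a cumulative reading cures. It is a hazard only for staff who use the body lists alone, which is easy to do because those lists sit in the enrolment section itself. The reply does not help with sitting, where the two texts give opposite answers for the same infant.

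Practical risk is also lower than the bare count suggests. The children are inpatients, the study team reviews the diagnosis before enrolment (8.7.2), and eligibility is assessed at a screening interview (8.7.3). Carers are counselled against QT-prolonging drugs (8.7.7.2), and 14.5.4 describes the QTc effect as mild and the arrhythmia risk as low. All of this is fair mitigation, but none of it puts the criterion back.

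A reader might infer three further things that the documents do not support:
- That the plan means to admit children with heart disease. No text does so, and the sections that address the matter exclude them.
- That only untreated heart conditions escape the body list. Section 8.7.7.2 bars some cardiac drugs, such as diuretics and antiarrhythmics, so a child on any other cardiac treatment is equally uncaught.
- That every 6-month period should become 3.5 months, as in 8.10. The 6 months in 8.8 is a follow-up period for children off study drug, and Table 2 schedules surveillance to 26 weeks. Shortening these would change safety follow-up and child-time for the incidence outcomes.

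The residence texts could also be read as serving different purposes, one about where the child lives and another about travel. That weakens the claim of three versions of one rule. It does not remove the mismatch between 4.1 and 8.7.6.2, or the wrong gloss within 4.1.

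**Conclusion.** The point holds as a defect in the eligibility text that should be fixed. The body lists lack the heart/QTc exclusion (0 of 20 items, against 3 mentions of heart conditions and 1 of family QTc history in 4.1–4.2). They also make the sitting rule unconditional, in direct conflict with 4.1. No text settles precedence.

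The enrolment risk for the heart/QTc child rests on one assumption: that staff use the body lists without 4.1. The refusal of infants who do not yet sit follows both from the body lists alone and from applying all lists together. The documents give no basis for the number of children in either group. The CRF is not shown, so its checklist may or may not carry the missing item. No effect on power, estimates or analysis is claimed.

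**What to change.** 1. In 8.7.4.4, replace the duplicate exclusion 10 with "Known heart conditions, or family history of congenital prolongation of the QTc interval".
2. In inclusion 5 of 8.7.4.4, restore the 4.1 qualifier, so that the rule covers only older children who could sit before admission.
3. State that 8.7.4.4 as corrected governs, and align 4.1, 4.2 and the CRF eligibility checklist to it. That includes the fever and prior-drug exclusions, the sickle cell wording and the haemoglobin condition in 4.2.
4. Choose one residence threshold for 4.1, 8.7.4.4 exclusion 5 and 8.7.6.2. If it stays at 25% of 14 weeks, the gloss should read 3.5 weeks.
5. Choose one eligibility window for other trials and surgery in 4.1 and 8.7.4.4. Leave the 6-month follow-up in 8.8 and the 26-week surveillance in Table 2 outside this edit.

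The cost is amendment wording, the ethics submission that 14.2 requires for any amendment, and a check of the CRF checklist. Limited in this way, the change affects neither sample size nor analysis.

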## 4.2 Narrative Protocol Summary

**Title:** Malaria Chemoprevention with monthly treatment with dihydroartemisinin-piperaquine for the post-discharge management of severe anaemia in children aged less than 5 years in Malawi: A 3-year, single site, parallel-group, five-arm cluster randomised trial of community versus health facility-based delivery mechanisms with or without mobile phone SMS reminders

**Short Title:** Post-discharge Malaria Chemoprevention Delivery (PMC) study

**Background and rationale:** Children hospitalised with severe anaemia in Africa are at high risk of readmission or death within 6 months after discharge. No strategy specifically addresses this post-discharge period. In Malawi, 3 months of post-discharge malaria chemoprevention (PMC) with monthly 3-day treatment courses of artemether-lumefantrine (AL) in children with severe malarial anaemia prevented 31% of deaths and readmissions. The effect was in addition to the effect of insecticide-treated bednets. There is now need to design and evaluate effective delivery mechanism for PMC within the health system.

**Objectives:** The primary objective of the trial is to determine the optimum PMC delivery mechanism by comparing community- versus health facility-based strategies in order to inform policy

**Study Type:** This is a single-centre, matched, cluster randomized, 5-arm, factorial design trial comparing the uptake of PMC-DHP delivered through health facility or community-based approaches with or without SMS/HSA reminders.

**Site:** 90 villages in the catchment areas of Zomba Central hospital in southern Malawi

**Study Population:** Inclusion criteria: convalescent children aged less than 5 years and weighing >5 kg admitted with severe anaemia (haemoglobin <5g/dL / Ht <15%); clinically stable, able to take or switch to oral medication; post-transfusion Hb >5g/dL. Exclusion criteria: blood loss due to trauma, malignancy, known bleeding disorders or sickle cell trait, known hypersensitivity to study drug, known heart conditions, non-resident in study area, previous participation in study, known need at enrolment for prohibited medication and scheduled surgery during the course of the study. HIV infection and cotrimoxazole prophylaxis are not exclusion criteria

**Study Interventions:** All children will receive Dihydroartemisinin-piperaquine (3-day treatment courses, given 2, 6 and 10 weeks after discharge) either: a) at discharge + SMS Reminder; b) at discharge + No SMS Reminder; c) at discharge + HSA Reminder; d) at OPD + SMS Reminder; or e) at OPD + No SMS Reminder

**Outcome Measures:** Primary: 100% of PMC drugs uptake (defined as administration of **all** 3-day treatment courses, given 2, 6 and 10 weeks after discharge) assessed by unannounced spot checks.

**Follow-up procedures:** Children will be followed up for 15 weeks by passive case detection in 2 phases: Pre-PMC (2 weeks between hospital admission and 2 weeks post-discharge); PMC (2-14 weeks post-discharge)

**Sample Size:** A sample size of 75 children per arm (375 total children) allows for a detection of 25% increase in uptake from 50% to 75% with 10% loss to follow-up (power 90%,  $\alpha=0.05$ ).

**Data Analysis:** The % of children receiving IPTpd according to schedule will be compared by relative risks (95% CI), adjusted for prognostic factors at baseline using log binomial or Poisson regression with adjustment for cluster effects

**Partner Institutions:** University of Bergen; Makerere University; KEMRI-CDC, Kenya; University of Minnesota; Liverpool School of Tropical Medicine; London School of Hygiene & Tropical Medicine; Imperial College London; University of Amsterdam; US Centers for Disease Control and Prevention, University of North Carolina, and University of Massachusetts.

Table1 : Study treatment and phases

| [figure not shown] |                                                     |                                                                                                                                                                                                                              |
|-------------------------------------------------------------------------------------|-----------------------------------------------------|------------------------------------------------------------------------------------------------------------------------------------------------------------------------------------------------------------------------------|
| Period                                                                              | Pre-PMC                                             | PMC                                                                                                                                                                                                                          |
| Trial intervention                                                                  | AL near discharge, all arms                         | Gp1: PMC Drugs at discharge + No SMS Reminder
Gp2: PMC Drugs at discharge + SMS Reminder
Gp3: PMC Drugs at discharge + HSA Reminder
Gp4: PMC Drugs at OPD + No SMS Reminder
Gp5: PMC Drugs at OPD + SMS Reminder |
| Rescue Rx acute malaria                                                             | Oral QN, 7 days                                     | AL, 3 days                                                                                                                                                                                                                   |
| Treatment for severe malaria                                                        | Parenteral artesunate / quinine and oral AL, 3 days |                                                                                                                                                                                                                              |

An end of study assessment will be done 14 weeks (3.5 months) after discharge.  
 AL=artemether-lumefantrine. PMC=Post-discharge Malaria Chemoprevention.  
 DP=dihydroartemisinin-piperaquine. QN=quinine

Table 2: Study Design and Schedule of Assessment

| Phase                       | Screening Phase         |                               | In-patient Hospitalisation phase | Enrolment & Randomisation | PMC Treatment Phase
12 weeks period from 2-14 weeks |                                     |                                      |                          |          |          |           |           |           | Post-intervention |
|-----------------------------|-------------------------|-------------------------------|----------------------------------|---------------------------|--------------------------------------------------------|-------------------------------------|--------------------------------------|--------------------------|----------|----------|-----------|-----------|-----------|-------------------|
| Location                    | In-Hospital             |                               |                                  | Clinic                    | Home/OPD                                               |                                     |                                      |                          |          |          |           |           |           | Clinic            |
| Visit number                | Pre-study Screening     | Screening Consent & Base-line | #1
t=0 weeks;
Allocation   | #2
t=2 weeks;
DHP 1 | #3
t=6 weeks
DHP 2                               | #4
t=10 weeks
DHP 3           | #5
Study end visit                | 14 wks
(day 98 +/- 7) |          |          |           |           |           |                   |
| Visit description           |                         |                               |                                  |                           |                                                        |                                     |                                      |                          |          |          |           |           |           |                   |
| Study Time                  |                         |                               |                                  |                           |                                                        |                                     |                                      |                          |          |          |           |           |           |                   |
|                             | Days -4 a -0 | Day0                          |                                  |                           | 2 weeks (day 14 +/- 3) c                    | 6 weeks (day 42 +/- 4) c | 10 weeks (day 70 +/- 4) c |                          |          |          |           |           |           |                   |
|                             |                         |                               |                                  |                           | 2w- Day 1                                              | 2w- Day2                            | 2w- Day3                             | 6w- Day1                 | 6w- Day2 | 6w- Day3 | 10w- Day1 | 10w- Day2 | 10w- Day3 |                   |
| Recruitment          |                         |                               |                                  |                           |                                                        |                                     |                                      |                          |          |          |           |           |           |                   |
| Pre-screening eligibility   | X                       |                               |                                  |                           |                                                        |                                     |                                      |                          |          |          |           |           |           |                   |
| Prior consent discussion    | X                       |                               |                                  |                           |                                                        |                                     |                                      |                          |          |          |           |           |           |                   |
| Enrolment            |                         |                               |                                  |                           |                                                        |                                     |                                      |                          |          |          |           |           |           |                   |
| Eligibility screen          |                         | X                             |                                  |                           |                                                        |                                     |                                      |                          |          |          |           |           |           |                   |
| Informed Consent            |                         |                               |                                  | X                         |                                                        |                                     |                                      |                          |          |          |           |           |           |                   |
| Study code issued           |                         |                               |                                  | X                         |                                                        |                                     |                                      |                          |          |          |           |           |           |                   |
| Allocation                  |                         |                               |                                  | X                         | X                                                      |                                     |                                      |                          |          |          |           |           |           |                   |
| Interventions        |                         |                               |                                  |                           |                                                        |                                     |                                      |                          |          |          |           |           |           |                   |
| Drugs at discharge + No SMS |                         |                               |                                  |                           | X                                                      | X                                   | X                                    | X                        | X        | X        | X         | X         | X         |                   |
| Drugs at discharge + SMS    |                         |                               |                                  |                           | X                                                      | X                                   | X                                    | X                        | X        | X        | X         | X         | X         |                   |
| Drugs at discharge + HSA    |                         |                               |                                  |                           | X                                                      | X                                   | X                                    | X                        | X        | X        | X         | X         | X         |                   |
| Drugs at OPD + No SMS       |                         |                               |                                  |                           | X                                                      | X                                   | X                                    | X                        | X        | X        | X         | X         | X         |                   |
| Drugs at OPD + SMS          |                         |                               |                                  |                           | X                                                      | X                                   | X                                    | X                        | X        | X        | X         | X         | X         |                   |
| Iron supplement.            |                         |                               |                                  |                           | Iron for 28 days from t=14-42 days                     |                                     |                                      |                          |          |          |           |           |           |                   |

| Phase | Screening Phase |  | In-patient Hospitalisation phase | Enrolment & Randomisation | PMC Treatment Phase
12 weeks period from 2-14 weeks |  |  |  |  |  |  |  |  | Post-intervention |
|-------|-----------------|--|----------------------------------|---------------------------|--------------------------------------------------------|--|--|--|--|--|--|--|--|-------------------|
|-------|-----------------|--|----------------------------------|---------------------------|--------------------------------------------------------|--|--|--|--|--|--|--|--|-------------------|

| Location                                   | In-Hospital             |                               | Clinic                | Home/OPD                                                                                                                                                                  |          |          |                      |          |          |                         |           |           | Clinic                |
|--------------------------------------------|-------------------------|-------------------------------|-----------------------|---------------------------------------------------------------------------------------------------------------------------------------------------------------------------|----------|----------|----------------------|----------|----------|-------------------------|-----------|-----------|-----------------------|
| Visit Number                               |                         |                               | #1                    | #2                                                                                                                                                                        |          |          | #3                   |          |          | #4                      |           |           | #5                    |
| Visit description                          | Pre-study Screening     | Screening Consent & Base-line | t=0 weeks; Allocation | t=2 weeks; DHP 1                                                                                                                                                          |          |          | t=6 weeks DHP 2      |          |          | t=10 weeks DHP 3        |           |           | Study end visit       |
| Study Time                                 | Days -4 a -0 | Day0                          |                       | 2 weeks (day 14 +/- 3)                                                                                                                                                    |          |          | 6 wks (day 98 +/- 7) |          |          | 10 weeks (day 70 +/- 4) |           |           | 14 wks (day 98 +/- 7) |
|                                            |                         |                               |                       | 2w- Day1                                                                                                                                                                  | 2w- Day2 | 2w- Day3 | 6w- Day1             | 6w- Day2 | 6w- Day3 | 10w- Day1               | 10w- Day2 | 10w- Day3 |                       |
| Assessments                         |                         |                               |                       |                                                                                                                                                                           |          |          |                      |          |          |                         |           |           |                       |
| Copy Clinic/Lab data from hospital records |                         | X                             | X                     |                                                                                                                                                                           |          |          |                      |          |          |                         |           |           |                       |
| Physical Exam.                             |                         | X                             | X                     |                                                                                                                                                                           |          |          |                      |          |          |                         |           |           | X                     |
| Blood sample                               |                         |                               | X c        |                                                                                                                                                                           |          |          |                      |          |          |                         |           |           |                       |
| MPs, Hb                                    |                         |                               |                       |                                                                                                                                                                           |          |          |                      |          |          |                         |           |           |                       |
